# Recovery of balance and walking in people with ataxia after acute cerebral stroke: study protocol for a prospective, monocentric, single-blinded, randomized controlled trial

**DOI:** 10.3389/fstro.2024.1388891

**Published:** 2024-08-05

**Keywords:** ataxia, acute stroke, coordination exercises, postural control, balance, walking

## Abstract

**Introduction:**

Posterior circulation stroke can lead to ataxia, manifesting in a loss of coordination and balance. Patients experience difficulty in activities of daily living and an increased risk of falling, both profoundly affecting quality of life. In individuals with neurodegenerative diseases, coordination exercises have been shown to lead to a reduction in ataxic symptoms. There is, however, limited evidence on the effect of physical therapy, specifically coordination exercises in patients with stroke-related ataxia. We therefore present a study protocol for a prospective trial.

**Methods:**

The purpose of this trial is to investigate the effects of coordination exercises compared to standard physiotherapy on balance and walking in ataxic stroke patients. Therefore, a prospective, single-blinded randomized controlled trial is currently ongoing at the Clinical Department of Neurology, Medical University of Innsbruck, Austria, in collaboration with two local rehabilitation facilities in Austria, Hochzirl Hospital and the Clinic for Rehabilitation Münster. Balance is the primary outcome of the study as assessed using the Berg Balance Scale. Secondary outcomes are concerned with walking, risk and number of falls, independence in daily life, and quality of life, rated using appropriate scales and scores. Patients are allocated applying a 1:1 ratio and a stratified block randomization. In both groups recruited individuals undergo five 45-min treatment sessions per week, totaling 20 sessions of coordination exercises (IG) or standard physiotherapy (CG) over the course of 4 weeks. Data is collected at the baseline (T0), after the 4-week supervised practice (T1), and after another 8 weeks of independent home-based training (T2).

**Discussion:**

This is the first randomized controlled trial investigating the effects of coordination exercises on balance and walking in people with stroke-related ataxia. As stroke guidelines emphasize the limited evidence of treatment for ataxic symptoms, this study aims to contribute further knowledge regarding tailored interventions for these patients.

**Clinical Trial Registration:**

German Clinical Trials Registry (drks.de). Identifier: DRKS00020825.

## 1 Introduction

The worldwide yearly incidence of stroke is 16.9 million, with ataxia being one of the most common symptoms when the vertebrobasilar system is affected (Feigin et al., 2014). Most frequently, infarction of the superior cerebellar artery (SCA), the posterior inferior cerebellar artery (PICA), or the anterior inferior cerebellar artery (AICA) lead to deficits in coordination (Kim and Caplan, 2016). Ataxia can also manifest in a loss of balance, gait ataxia, dysmetria, dysarthria, and nystagmus. Gait ataxia is evidenced by a staggering gait pattern, irregular foot placement and stride length, and an increased stance width (Cabaraux et al., 2023). When balance impairment is severe, it significantly hampers an individual's ability to perform activities of daily living. The loss of balance and coordination increases the risk of falling, which is severely impacting quality of life (Belas Dos Santos et al., 2018).

Still, research on physical therapy approaches for patients with ataxia after stroke is scarce (Kruger et al., 2007; Marquer et al., 2014; Intercollegiate Stroke Working Party, 2023). Previous studies have investigated treatment approaches such as treadmill training (Bultmann et al., 2014), robot-assisted gait training (Kim et al., 2019), trunk exercises (Stoykov et al., 2005), or a combination of balance and walking exercises (Kruger et al., 2007). Unfortunately, these methods did not demonstrate a significant effect on coordination (Bultmann et al., 2014).

Most of the studies on rehabilitation of people with ataxic symptoms have been conducted in patients with degenerative diseases, like Friedreich's ataxia, multiple sclerosis, or degenerative cerebellar ataxia. In contrast to the studies in stroke-related ataxia mentioned above, most of these trials primarily involved coordination exercises and yielded promising results, reducing the progression of ataxic symptoms (Ilg et al., 2009, 2010, 2012; Miyai et al., 2012; Synofzik et al., 2013; Sartor-Glittenberg and Brickner, 2014). Another strength of coordination exercises was their easy applicability into clinical physical therapy practice (Brötz et al., 2007; Ilg et al., 2010; Marquer et al., 2014). Given that coordination exercises showed symptom reduction in patients with progressive diseases, it seems plausible to anticipate effects in patients with ataxia after stroke. The feasibility of incorporating coordination exercises into rehabilitation of acute stroke patients has already been shown in a pilot trial (Meier et al., 2021). These results underscore the need for a randomized controlled trial to explore their effectiveness with an appropriate number of participants.

## 2 Methods and analysis

### 2.1 Aims and design

A prospective, single-blinded, randomized controlled trial (RCT) is currently being conducted in a monocentric setting in Austria. The aim is to investigate the effects of coordination exercises compared to standard physiotherapy, on balance and walking in patients who suffer from stroke-related ataxia.

### 2.2 Study setting

The initial phase of the study is conducted on the stroke unit at the Clinical Department of Neurology, Medical University of Innsbruck, Austria, which includes a large, comprehensive stroke center. The second study phase is performed at the rehabilitation facility Hochzirl Hospital, Austria, or the Clinic for Rehabilitation Münster, Austria, as patients are usually transferred to a rehabilitation facility 2 weeks after a stroke. The choice of the rehabilitation facility and the timing of the transfer can differ based on individual requirements and the capacities of the rehabilitation facilities.

### 2.3 Participants

Patients are recruited at the Clinical Department of Neurology, Medical University of Innsbruck, Austria. All patients who are admitted due to an acute stroke are evaluated for eligibility. If the patient meets all inclusion criteria and none of the exclusion criteria, the investigator will seek an informative briefing with prospective subjects concerning the study details and a written informed consent is obtained prior to study enrolment.

#### 2.3.1 Inclusion criteria

People who are at least 18 years of age, who experienced an acute ischemic or hemorrhagic stroke (identified by MRI/CT), and who suffer from gait ataxia are eligible, if they score at least 1 point on the items gait, stance, trunk or heel-shin-slide of the Scale for the Assessment and Rating of Ataxia (SARA; Schmitz-Hübsch et al., 2006) and 47 points or less on the Berg Balance Scale (BBS; Stevenson, 2001).

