### 2.5 Data collection

Data is collected at the baseline (T0 assessment), after the 4-week phase of supervised practice (T1 assessment) and after 3 months (T2 assessment; Table 1). T0 and T2 assessments take place at the Clinical Department of Neurology, Medical University of Innsbruck, Austria. T1 assessment is conducted in the patients' rehabilitation facility. Demographic data (age, sex) and stroke-specific data (location, type, lesion side, and timepoint) are extracted from medical records. Outcomes of balance, walking, ataxia, and fear of falling are obtained from trained assessors.

Personal data is pseudonymized using a patient identification number (ID) and only pseudonymized data is transferred to statistical analyses. To ensure the plausibility and integrity of the data, random data checks (value range, field type, and logic checks) are performed, and the CRF data is entered into the database by two independent researchers.

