### 2.7 Statistical analysis

IBM SPSS software, release 29.0 (IBM Corporation, Armonk, New York, USA), R software version 4.3.2 (R Foundation for Statistical Computing, Vienna, Austria) and GraphPad Prism 10 (San Diego, California, USA) will be used for the data analyses. Descriptive statistics are used for the baseline demographic variables, primary and secondary outcomes. Continuous data is checked for significant outliers using studentized residuals and a normal distribution using the Shapiro Wilk Test, Q-Q plots, and histograms. Frequencies [number (N), %] are presented for counted (N falls, N adverse events if any, N of home exercises) and nominal data (gender, stroke etiology and location, and rehabilitation facility). Medians (interquartile range) are reported for ordinal data (mRS, BBS, FGA, TCT, FES-I, FRT, EQ-5D-3L, SARA, and SINGER), and mean (SD) is reported for continuous data (age, time after stroke, TUG, and posturography outcomes).

The significance level is defined by a two-tailed *p*-value of <0.05. Baseline (T0) between-group differences are evaluated using Fisher's exact test for nominal data, Mann Whitney-*U*-test for ordinal data and independent samples *t*-test for continuous data. If the distribution is non-normal in continuous data, data transformation or non-parametric statistics are performed, as appropriate. To evaluate within-group differences between T0, T1, and T2 measures, for ordinal data, Friedman test is utilized followed by Dunn's multiple comparisons test for pairwise comparisons. To examine between-group differences, using newly created variables (T1 or T2 minus T0 values), a Mann Whitney-*U*-test is performed. For continuous data, test assumptions for a repeated-measures analysis of variance (ANOVA) are checked (e.g., normality, sphericity) and dealt with as appropriate. If the requirements are met, repeated measures ANOVA are performed, with “time” (T0, T1, and T2 measurements) as the within-subject factor, “group” (IG, CG) as the between-subject factor, and adjusted for the stratification variables (age, sex). If statistical significance is present, a *post-hoc* analysis of pairwise comparisons between measurement time points is performed, followed by a *post-hoc* Bonferroni correction for multiple comparisons. An intention-to-treat analysis is performed analyzing all study participants in the groups which they have been assigned to.

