However, there are also limitations to consider in this study. Firstly, the study is conducted in a rehabilitation setting where patients receive additional individualized therapies. These supplementary therapies could potentially influence the study results, making it challenging to exclusively attribute the observed effects to the specific intervention under investigation. Secondly, as the trial focuses on acute stroke patients who undergo rapid recovery, selecting a timely and appropriate balance assessment over the 3-month study period is challenging due to the potential ceiling effect. To address this concern, the researchers chose 47 points or fewer in BBS as an inclusion criterion to ensure the detection of significant changes from T0 to T1 (Stevenson, 2001) and included the FGA to demonstrate effects during the sub-acute stages (T1 to T2). This limitation is relatively minor since the primary objective of the study is to evaluate the impact of supervised therapy sessions from T0 to T1. Thirdly, the initial training of therapists conducting the interventions had to be performed online because of the COVID-19 pandemic. This adjustment in training methods may influence the delivery and consistency of the therapy sessions. However, therapists have the option to watch the recording of the training, whenever they feel it is necessary to refresh certain aspects.

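### The primary BBS comparison is an unadjusted Mann-Whitney test that leaves out time from stroke to T0, a recorded and plausibly prognostic variable; the cost is precision, not bias

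*Protocol article*

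**What the plan says.** Section 2.3.1 admits adults "who experienced an acute ischemic or hemorrhagic stroke (identified by MRI/CT), and who suffer from gait ataxia are eligible", subject to ataxia and BBS scores. Section 2.5 places T0 in the acute department: "T0 and T2 assessments take place at the Clinical Department of Neurology". Section 2.2 adds that "patients are usually transferred to a rehabilitation facility 2 weeks after a stroke" and that "the timing of the transfer can differ based on individual requirements and the capacities of the rehabilitation facilities". The article gives no distribution of the interval from stroke to T0.

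Table 1 and section 2.5 show that the time of the stroke is collected. Section 2.3.3 stratifies by age and gender only.

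Section 2.7 lists time after stroke among the variables summarised by mean (SD): "continuous data (age, time after stroke, TUG, and posturography outcomes". As a continuous variable it also falls under the baseline between-group t-test. BBS is classed as ordinal, so its groups are compared by Mann-Whitney U "using newly created variables (T1 or T2 minus T0 values". The repeated-measures ANOVA for continuous outcomes adjusts for age and sex, not for time since stroke. The Discussion names T0 to T1 as the period of primary interest and says that "the trial focuses on acute stroke patients who undergo rapid recovery".

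**The concern.** If balance recovers quickly at first and then more slowly, a four-week gain measured from an early T0 is larger than one measured from a late T0, in either arm. Variation in T0 timing is then a source of variance in the primary change score. A chance difference between arms in mean T0 day also moves the estimate, and the stated test has no means of correcting it. The baseline t-test may show the imbalance but does not adjust for it. At stake is precision in a trial of 33 evaluable patients per group, when the variable that could recover some of it is already recorded.

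**Working it through.** **The plan's own figure.** From section 2.6, with equal weights:
- Pooled SD = sqrt((2.08² + 4.73²)/2) = 3.654; times 1.442 = 5.27.
- Difference = 17.33 − 13.67 = 3.66.
- n per group = 2 × (1.960 + 0.842)² × 5.27² / 3.66² = 32.5, so 33 per group and 66 in all. The stated figure is reproduced.
- An exact two-sided t-test with 33 per group has power 0.79.

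**What is already in the standard error.** The 95% range of the estimated difference is ±1.96 × 5.27 × sqrt(2/33) = ±2.5 points. Chance imbalance in T0 timing is part of this range, not an addition to it.

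**Assumptions.** The documents give neither a spread of T0 days nor a recovery curve. I took BBS(t) = 56 − u − D·exp(−kt), with:
- D uniform on 10-50 and u exponential with mean 2 or 6;
- k lognormal (log-SD 0.3 or 0.6) around 1/14, 1/21 or 1/28 per day;
- measurement SD 1.5, and only patients with T0 BBS of 47 or less kept;
- T0 uniform on days 2-14 (12 settings), and on days 1-7 as the alternative.

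**Time alone.**
- Slope: the four-week gain falls by 0.49-0.98 points per day of later T0. As a cross-check, under exponential recovery the slope is gain/τ. If the control group's 13.67 is a four-week gain, that is 13.67/28 = 0.49 to 13.67/14 = 0.98.
- Variance of change explained: about 8-23% (days 2-14), or 2-8% (days 1-7).
- Power at 8%: SD = 5.27 × sqrt(0.92) = 5.05, power 0.83. At 23%: SD = 5.27 × sqrt(0.77) = 4.62, power 0.89.
- Chance imbalance: the SD of T0 day is about 3.45, so the 95% limit is 1.96 × 3.45 × sqrt(2/33) = 1.67 days. Times the slope, this is 0.8-1.6 points.

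**With T0 BBS also in the model (days 2-14).**
- T0 BBS alone explains 34-84% of the variance of change.
- T0 day adds a further 0.2-5.6% of total variance (at most 1.7% for days 1-7).
- The slope falls to 0.08-0.50 points per day. The chance-imbalance shift becomes 1.67 × 0.08 = 0.13 to 1.67 × 0.50 = 0.84 points, or 4-23% of 3.66.

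**Error rates.** A separate simulation used T0 on days 1-14, a linear loss of 0.5 points per day and no baseline BBS.
- Under no effect, the planned test rejected in 4.8% of runs and the mean estimate was about 0.
- In runs where the arms' mean T0 differed by more than about 1.4 days, it rejected in 8.6%, against 4.2% with time in a linear model.
- With a true effect of 3.66, power was 0.77 for Mann-Whitney and 0.84 for the adjusted model. Part of that gap is the rank test itself, since the unadjusted t-test has 0.79.

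**The case against.** The strongest reply is that nothing here is an error. Allocation is concealed until after T0, so timing is balanced on average, and any unmodelled prognostic factor is covered by the standard error. If 5.27 is the SD of change, it already contains timing variation, so adjustment is a gain rather than the repair of a shortfall. This stands. A reader might infer that the treatment effect is biased or that false positives are inflated overall; the 4.8% rejection rate and near-zero mean estimate show neither.

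A reader might also take the 0.8-1.6 points (22-44% of 3.66) as the harm. Most of that is the effect of T0 BBS, since patients assessed earlier tend to start lower; the part specific to timing is about half or less. The assumed spread may also be generous. Patients are screened on acute admission and treated on the stroke unit before a transfer at about two weeks, which points to earlier T0 days. The simulated SD of change (6.2-7.1) exceeds the plan's 5.27, so the power figures borrow only the share of variance explained.

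It is tempting to say that the trial lacks an onset window. The article does not state one, but it condenses a full protocol that is not shown and may contain it. Recruitment at an acute department also bounds the interval in practice. That reading is not supported. Nor is it right that time since stroke is merely described, because section 2.7 also tests it at baseline.

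What the reply does not remove is that section 2.7 states the primary comparison and the adjustment set used elsewhere, and time since stroke is in neither.

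**Conclusion.** The point holds as a matter of efficiency. The stated primary test ignores a recorded baseline variable that the article's own account of the population makes plausibly prognostic. The loss is modest: on its own the variable might lift t-test power from 0.79 to about 0.83-0.89 if T0 spreads over days 2-14, and by less if T0 falls on days 1-7. Beside T0 BBS it adds about 0.2-5.6% of total variance for days 2-14, with a 95% chance-imbalance shift of about 0.1-0.8 points. The larger gain comes from T0 BBS, which the same change of model would bring in. All sizes except the reproduced sample size and the ±2.5 points rest on the assumed recovery curve and T0 spread. The stated sample size need not change.

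**What to change.** Before unblinding, replace the primary Mann-Whitney comparison in section 2.7 with a pre-specified covariate model of T1 BBS on group, T0 BBS, age, sex and time from stroke to T0 (for example log days). Use ANCOVA, or a proportional-odds model if BBS is kept ordinal. Keep the Mann-Whitney test on change as a sensitivity analysis, and report the distribution of T0 timing by arm.

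The cost is that the stated primary test changes, which is more than adding a covariate because Mann-Whitney takes none. The ANCOVA would use six parameters with the intercept, leaving 66 − 6 = 60 residual degrees of freedom. No new data or patients are needed. Section 4 planned completion by the end of June 2024, and section 2.3.3 sets unblinding after completion. If the allocation is already open, the model should be reported as a post hoc sensitivity analysis and labelled as such.

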#### 2.3.2 Exclusion criteria

Exclusion criteria are a modified Rankin Scale (mRS) score of 5 or more (Rankin, 1957), a previous stroke leading to persistent debilitating neurological deficits defined as an mRS score of 3 or more, a comorbidity that limits active study participation (e.g., life expectancy of <3 months, alcohol or drug abuse), physical or mental conditions that would not allow safe participation in the study or would influence the assessment of outcomes (e.g., dementia, cardiac insufficiency, severe aphasia, etc.), or pregnancy.

#### 2.3.3 Randomization, allocation, and blinding

Participants are randomly allocated into one of two groups. Group allocation uses a 1:1 ratio to either control group (CG) or intervention group (IG) utilizing stratified blocked randomization and hidden block sizes. The allocation sequence is generated using an online randomization software (Sealed Envelope Ltd., London, UK; Sealed Envelope Ltd., 2022). Stratification variables are age (≤ 70 years, >70 years) and gender (male, female).

Allocation concealment is conducted, as an independent researcher in charge for the randomization does not disclose patients' group allocation until after the baseline assessment (T0). To effectively conceal the randomization sequence, sequentially numbered, opaque sealed envelopes are used. After T0 assessment, department staff who are independent of assessment and intervention assign the patient to the appropriate group using the sealed envelopes. The staff then informs the therapist responsible for providing the assigned intervention.

Outcome assessors are blinded to patients' group assignment. Patients are informed that an examination of the effects of two distinct physiotherapy exercise programs is performed. However, they remain unaware of the precise details of the interventions of both groups and the study's rationale. Patients are encouraged not to talk to the assessor about the exercises. The planned time for regular unblinding is after study completion.

### 2.4 Intervention

Physical therapy sessions start after T0 assessment in both groups. Over the course of 4 weeks patients receive 20 supervised therapy sessions, five 45-min sessions per week, in addition to multidisciplinary rehabilitation treatment (Table 1).

**Table 1 T1:** Schedule of enrolment, interventions, and assessments.

		**T0^a^**	**W1–W4**	**T1^b^**	**W5**	**W6**	**W7**	**W8**	**W9**	**W10**	**W11**	**W12**	**T2^c^**
Enrolment	Eligibility screen	X											
	Informed consent	X											
	Group allocation	X											
Data collection	Demographic data^d^	X											
	Stroke location, type, lesion side, and timepoint	X											
	Duration of rehabilitation stay												X
	mRS	X		X									X
	SARA	X		X									X
	BBS	X		X									X
	TCT	X		X									X
	FES-I	X		X									X
	Posturography: TYMO^®^	X		X									X
	FRT	X		X									X
	FAC	X		X									X
	TUG	X		X									X
	FGA			X									X
	SINGER			X									X
	EQ-5D-3L			X									X
	MRI^e^	X											X
	Adherence evaluation^f^					X		X		X			X
	Number of falls		X		X	X	X	X	X	X	X	X	
	Adverse events		X		X	X	X	X	X	X	X	X	
Intervention	Supervised intervention		X										
	Homebased intervention		X		X	X	X	X	X	X	X	X	

^a^Assessment at baseline.

^b^Assessment after 4-week intervention.

^c^Assessment after 8 weeks of home exercise.

^d^Demographic data include age and sex.

^e^Patients with cerebellar infarction (according to amendment).

^f^Phone calls in week 6, 8, and 10 and return of the checklist in week 13.

W, week; mRS, modified Rankin Scale; SARA, Scale for the Assessment and Rating of Ataxia; BBS, Berg Balance Scale; TCT, Trunk Control Test; FES-I, Falls Efficacy Scale International; FRT, Functional Reach Test; FAC, Functional Ambulation Categories; TUG, Timed Up and Go; FGA, Functional Gait Assessment; SINGER, Scores of Independence for Neurologic and Geriatric Rehabilitation; EQ-5D-3L, EuroQol five dimensions questionnaire; MRI, Magnetic resonance imaging.

Coordination exercises (intervention group, IG) are compared to standard physiotherapy (control group, CG) i.e., state of the art treatment according to clinical guidelines, that patients receive in a clinical routine.

Exercises in both groups are consolidated into an exercise program, which aids in selecting the appropriate exercises depending on the severity of the symptoms (see Sections 2.4.1 and 2.4.2). Typically, exercises for patients with more severe symptoms are listed at the beginning of the program with lower numbers, gradually advancing in difficulty as the numbers increase. Conversely, exercises for individuals with milder impairments are positioned further in the program with higher numbers, reflecting a progression toward more challenging tasks.

